Although one-to-one randomisation will be used, this will done in blocks of 24 (12 control and 12 PLH-YC) and vary in implementation for Republic of Moldova compared to Romania and North Macedonia. In the Republic of Moldova, participants within each of the 12 recruitment sites will be randomly allocated to either the control or the intervention due to the geographical spread of the sites across the country. In Romania and North Macedonia, participants will be assigned to any PLH-YC programme or any control lecture group and not based on region, but rather based on scheduling availability.

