##### Intervention group

The optimised version of PLH-YC will be delivered over five weekly sessions using a participatory, non-didactic approach to engage parents in learning positive parenting and child behaviour management skills. Programme activities include illustrated comics modelling how to implement key parenting skills, home activity assignments to apply these skills with their children, and group discussions addressing challenges experienced when applying home activities. The programme also includes simple mindfulness stress reduction exercises such as “Taking a Pause” to help parents cope with stress and reactivity towards their children. There is a facilitator manual for each session, and parents receive a PLH parent book (long versions in English, Macedonian, and Romanian available here: https://rise-plh.eu/work-packages/work-package-2/). For the current study, the facilitator manuals and parent handbooks of the optimised intervention will also be translated into Albanian and Russian. If the programme is delivered in person according to the standard protocol, each PLH-YC group with 12 parents will be delivered by two facilitators. Locally recruited professionals and non-professionals (e.g. teachers, psychologists, social workers, and peer parents) with prior experience delivering the programme during Phase 2 of the RISE project will serve as facilitators. All facilitators participated in a 40-h standardised training prior to delivering the programme for the first time. They will also receive an additional 16-h booster training prior to the RCT.

Programme and lecture delivery will start as soon as the programme implementers can organise a group of approximately 12 participants per condition who have completed baseline assessments. Facilitators of both groups will receive supervision on demand by trained coaches who have also previously provided coaching to facilitators during Phase 2.

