#### Data analysis

##### Sample size calculation

To allow detection of small effect sizes, we will estimate sample size based on a *d* = .25 (*f* = .10) for the primary outcomes. Detecting this effect in a repeated measures ANOVA at an alpha of .05 whilst ensuring a power of 80% requires a total sample of *N* = 704. We will examine the change in the primary outcomes across three time points (pre, post, and follow-up) within the overall sample using latent growth modelling and conduct a multi-group analysis to test differences across countries. To reach the required sample size of 704, we will recruit a total of 864 families for baseline assessment, assuming approximately 17% drop-out rate based on our previous phase of data collection [69].

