##### Primary and secondary outcome analyses

Data will be analysed using an intention-to-treat approach, in line with the study protocol and with good practice in RCTs [70]. Missing data will be handled using either multiple imputation or Full Information Maximum Likelihood (FIML) method [71].

The primary analysis will consist of testing comparatively the magnitude of change in child aggresive behaviour, in the control vs. PLH-YC participants, at post-test and follow-up. Identical analyses will be run for the secondary outcomes (i.e. child internalising problems, dysfunctional parenting strategies, positive parenting, daily reports of effective parenting behaviour, child maltreatment, parental mental health, IPV, couple satisfaction, parenting stress, quality of parent-child relationship, and child ’s quality of life). The main analyses will involve testing pre-post or pre-follow-up differences controlling for pre-intervention levels whilst accounting for covariates. Maximum likelihood estimation with robust statistics will be used with Mplus 8.2 software to account for non-normal distributions in measures and also apply a FIML framework for handling missing data at post- or follow-up. The models will be further tested using latent growth curve models adjusting for country and pre-assessment levels of the outcome variables (e.g. age as a time-invariant covariate). Indirect effect models will be tested in a structural equation framework and include participation rate and fidelity as mediators for the PLH-YC group and enrolment rate as the mediator across groups. In additional analyses, we will also model the effects of participation (i.e., attendance). This will be analysed with Complier Average Cause Effect models that estimate the magnitude of the paths based on the baseline scores in predictors (e.g. family adversity) and actual participation [72]. Further clustering will be within groups (facilitators) and included in subsequent analyses as needed. The analyses for MINI-KID ODD/CD positive screen will be conducted with logistical regression models due to the categorical nature of the data. Depending on the distributions and on other descriptive indicators, Bayesian analyses will be used as deemed appropriate.

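### Both arms are delivered in groups, but group clustering is deferred out of the main outcome models and absent from the sample size, so at any positive ICC the main tests are too liberal and 80% power is not assured

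*Protocol article*

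**What the plan says.** **Delivery.** Under *Intervention group*, "each PLH-YC group with 12 parents will be delivered by two facilitators", over five weekly participatory sessions; delivery in either condition starts once about 12 participants can be assembled. The contingency plan allows PLH-YC groups of six with one facilitator, and keeps online lecture groups at 12. The lecture is a single session of 1 to 1.5 hours in which facilitators are trained to limit discussion (*Control group*).

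**Allocation.** Randomisation is individual, 1:1, in blocks of 24. In Moldova it takes place within each of 12 recruitment sites. In Romania and North Macedonia families join any group of their condition, "and not based on region, but rather based on scheduling availability" (*Group allocation and allocation concealment*).

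**Analysis.** Under *Primary and secondary outcome analyses*, the main models test change adjusted for the pre-intervention level and covariates, using robust maximum likelihood to deal with non-normality. MINI-KID ODD/CD is analysed by logistic regression. Clustering appears after the main, growth-curve, mediation and complier-average models: "Further clustering will be within groups (facilitators) and included in subsequent analyses as needed".

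**Sample size.** The section opens from the target effect: "we will estimate sample size based on a *d* = .25 (*f* = .10) for the primary outcomes". On that basis, with 80% power and a 5% alpha in a repeated measures ANOVA, it arrives at 704 families. Losses are then added: "we will recruit a total of 864 families for baseline assessment, assuming approximately 17% drop-out rate". No ICC, group size or design effect enters.

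**The concern.** Families who share five interactive sessions and the same facilitators are likely to have outcomes more alike than families in different groups. Filling groups by availability can add to this. A standard error that treats families as independent is then too small. Robust maximum likelihood does not repair this unless a cluster is declared, and the plan gives non-normality as its purpose.

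The authors recognise the clustering but place it outside the main analysis, on a condition with no criterion. The main CBCL and MINI-KID tests, and the secondary outcomes analysed in the same way, could therefore be reported with intervals that are too narrow. The choice of standard error also stays open until results can be seen.

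**Working it through.** **1. The plan's own figure, 704.** Two-sided alpha .05 is assumed (sidedness is not stated).
- Simple two-group comparison, 80% power: d = .25 needs 504; d = .20 needs 786.
- For two equal groups f = d/2, so d = .25 is f = .125, and f = .10 is d = .20. The stated pair is inconsistent, which is a separate point.
- Repeated measures ANOVA, between-group effect, f = .10, three time points, noncentrality f²·N·3/(1 + 2ρ): with ρ = .5, 526 gives 80% and 704 gives 90%. With ρ = .8, 684 gives 80%. The group-by-time interaction with ρ = .5 needs 164.
- No ρ is stated, so 704 does not follow from the stated inputs, although an undisclosed ρ near .8 would come close.
- Dropout: 704/.83 = 848.2, so 849; 864 implies 1 − 704/864 = 18.5% loss, close enough to the stated 17%.

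**2. Inputs for clustering.**
- Groups per arm: 864/2/12 = 36.
- Retained per group of 12: m = 12 × 704/864 = 9.78. Per group of six: 4.89.
- ICC: none in the document. Values of .02 and .05 are assumed, with .10 as a stress value.

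**3. Formulas.** Design effect in a clustered arm: 1 + (m − 1)·ICC. Variance ratio of the contrast, DE: mean of the two arms' design effects (1 for an unclustered arm). True error of the unclustered test: 2·[1 − Φ(1.96/√DE)].

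Worked case, ICC .05, both arms: DE = 1 + 8.78 × .05 = 1.439; √DE = 1.20; 1.96/1.20 = 1.634; error = 10.2%.

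| ICC | Clustering | DE | True error |
|---|---|---|---|
| .02 | PLH-YC only | 1.088 | 6.0% |
| .02 | both arms | 1.176 | 7.1% |
| .05 | PLH-YC only | 1.219 | 7.6% |
| .05 | both arms | 1.439 | 10.2% |
| .10 | PLH-YC only | 1.439 | 10.2% |
| .10 | both arms | 1.878 | 15.3% |

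PLH-YC groups of six at ICC .05: the PLH-YC arm has 1 + 3.89 × .05 = 1.194. With PLH-YC only, DE = 1.097 and the error is 6.1%. With lecture groups of 12 also clustered, DE = 1.317 and the error is 8.8%.

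A simulation (2,000 replicates per cell, 36 + 36 groups, 81.5% retained) agrees. At ICC .05 the unclustered test rejected a true null 7.4% of the time (PLH-YC only) and 9.0% (both arms). A cluster-robust test with 72 clusters rejected 4.7-5.0%.

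**4. Moldova.** Each site contributes both arms, so correlation shared across the arms cancels from the contrast. The variance factor there is 1 + (m − 1)·ρ_within − m·ρ_between, where ρ_between is the correlation between families of the same site in different arms. If the correlation is wholly site-level (ρ_within = ρ_between = ρ), it is 1 − ρ, and there is no inflation. Only the excess due to the delivery group inflates the error. This applies to 288 of 864 families.

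**5. Power at 704 when clustering is allowed for.** Power = Φ(λ/√DE − 1.96), both arms clustered, m = 9.78.

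| Base without clustering | λ | ICC .02 | ICC .05 |
|---|---|---|---|
| 80%, as stated | 2.80 | 73% | 65% |
| 90% (f = .10, ρ = .5) | 3.24 | 85% | 77% |
| 91% (d = .25, simple comparison) | .25·√(704/4) = 3.32 | 86% | 79% |

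From the 91% base, power stays at or above 80% while DE ≤ (3.317/2.802)² = 1.401. That is an ICC up to .401/8.78 = .046, or .401/11 = .036 with a full 12 per group.

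**The case against.** **Power.** A reader might infer that the trial misses its stated 80% power. The documents do not support that. The inference requires 704 to give exactly 80% for independent families, and 704 cannot be derived from the stated inputs. On other readings of those inputs there is slack that absorbs a modest ICC. Baseline adjustment could add more.

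**Standard errors.** They are too small only if the ICC is above zero, and the document gives none. The .10 rows are a stress case with no support in the text. Equal clustering in a single lecture with little discussion is a worst case, so the PLH-YC-only figures are probably nearer the mark. In Moldova the simple design effect overstates the problem to the extent that correlation belongs to the site. These limits all stand and are built into the size given here.

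**Left to the analysis plan.** The article does name the clustering unit, and a condensed article may leave the exact model specification to a fuller document. This stands only in part. The article is not silent: it assigns clustering to later analyses and makes it conditional. Followed as written, that rule gives main tests with family-level standard errors.

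**Conclusion.** The point holds in a conditional form. The main outcome models omit delivery-group clustering that the design creates and the authors acknowledge, and the sample size makes no allowance for it. At any positive net within-group correlation, the nominal 5% test is too liberal: about 6-7% at ICC .02 and 8-10% at ICC .05. These figures assume equal groups with 9.8 retained and a normal approximation. They are lower with PLH-YC groups of six, and where Moldovan site effects are common to both arms. The direction is firm; the size is uncertain because no ICC is stated.

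On power, the supportable conclusion is that 80% is not assured, since any margin is undocumented and could be used up at an ICC of a few hundredths.

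**What to change.** - Declare delivery group as the cluster in every primary and secondary outcome model, including the MINI-KID logistic models. Use either cluster-robust standard errors with the robust maximum likelihood already planned, or a nested model whose group variance may differ by arm.
- Keep recruitment site in the model for Moldova.
- Keep every family in its assigned group for analysis, whether or not it attended. State in advance how the cluster is defined where facilitators lead more than one group or pair differently across groups.
- Delete *as needed* and the deferral to subsequent analyses.
- Restate the power for 704 over a stated ICC range, giving group size, the correlation between time points and one consistent effect size.

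**Cost.** Wording and model specification, plus a group identifier in the analysis data. The *Trial status* section reports recruitment, delivery and post-assessment as complete, so the remedy is analytic and needs no more families. Intervals become slightly wider, and the stated power less favourable.

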##### Other subgroup analyses

To the extent to which we will have enough secondary caregivers (e.g. fathers) in the programme, it will be of interest to test whether parent gender acts as a moderator of programme effects on child reported behavioural and emotional problems. Child gender will also be included as a covariate in the models of outcome, testing both main effects and interactions between covariates and intervention.

Other subgroup analyses will explore, across and within countries, the role of different cultural, economic, and societal factors on the pre-specified outcomes. Particular attention will be given to vulnerable populations (ethnic minorities and/or economically disadvantaged groups) and whether intervention effects on outcomes will be similar to those for non-disadvantaged individuals. For instance, we aim to test the moderating role of parental (mental) health, ethnicity, poverty, and parenting practices (harsh parenting) on primary and secondary outcomes. Given the increased power required for moderation analyses, these analyses will be considered exploratory.

##### Cost-effectiveness analysis

The objective of this analysis is to evaluate the costs and cost-effectiveness of the PLH parenting programme vs. the lecture on parenting. Cost-effectiveness ratio will be calculated in terms of Euros per one point reduction of the CBCL aggressive subscale score in the PLH-YC programme. Besides the use of CBCL aggressive subscale score as the primary outcome for the cost-effectiveness analysis, other outcomes such as Parenting Scale (PS), Parenting of Young Children Scale (PARYC), and Quality of life (Child Health Utility 9D) will also be used to better inform decision making.

We will conduct cost analyses based on cost diaries and on cost estimations for participant access to alternative social/mental health services in each site. Programme costs will be calculated using a micro-costing approach, multiplying resource use by unit costs. Our micro-costing will be conducted from the payer’s perspective, excluding participants’ out-of-pocket costs and the opportunity costs associated with participant time. We are interested in the cost categories and the extent to which they vary across sites and subgroups. Cost-effectiveness ratio (outcomes expressed as natural health outcome units) and cost-utility ratio (outcomes expressed as quality-adjusted life years) will be calculated to assess and compare the cost-effectiveness of PLH-YC across sites and populations. Depending on data availability, either extended cost-effectiveness analysis (ECEA) or distributional cost-effectiveness analysis (DCEA) will be further conducted to incorporate equity into an economic evaluation of PLH-YC. ECEA provides breakdowns of the costs and outcomes of health interventions by social group. DCEA, in addition, provides a summary measure of equity impact and analyses the potential trade-offs between equity and efficiency impacts. Furthermore, based on the cost-effectiveness results, the resources required to provide the optimal PLH programme on a large scale will be estimated for North Macedonia, the Republic of Moldova, and Romania respectively, and barriers to broader implementation will be discussed.

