If the optimised programme is effective, a secondary objective of the RISE project is to explore the implementation and scalability of PLH-YC to enable wide-spread and sustained use of the optimised parenting programme in the Southeastern European countries. We will apply the steps of the RE-AIM model [38] to translate the learning from implementation of the evidence-based programme into sustainable practice. Moreover, we will report on the cost-effectiveness of the programme and other service use by parents in the PLH-YC and control conditions during, and after the intervention across the three countries.

The secondary aims and hypotheses are:
Examine the cost-effectiveness of PLH-YC in comparison to a lecture on parenting on the *primary outcome* of child aggressive behaviour and the economic impact of the programme, including potential costs for future dissemination and scale-up. Impact on other outcomes such as dysfunctional parenting, positive parenting, and child quality of life will also be used to better inform decision-making.To assess the role of socio-economic, contextual and individual factors (i.e. family adversity, parental mental health, intimate partner violence, couple dissatisfaction, and child aggressive behaviour at baseline) on the implementation of PLH-YC in the three countries. We will examine implementation in hypotheses a–c in two ways. We will examine these associations with enrolment (attended 1st session) across groups. We will also examine the associations with participation rate in the PLH-YC condition (percentage of sessions attended). The hypotheses are:

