### Participants and eligibility criteria

Potential parents or other primary caregivers will have the following inclusion criteria: (a) be aged 18 years or older, (b) be responsible for the care of a child between the ages of 2 and 9; (c) report at least subclinical levels of child’s behavioural problems as assessed with the oppositional defiant disorder subscale (ODD) of the Child and Adolescent Behavior Inventory (CABI, scores ≥ 10 will be included) [41, 42]; (d) have spent at least four nights a week with the child in the same household during the previous month and will continue to do; (e) agree to being randomised to one of the conditions; (f) consent to participate in the full study; (g) have adequate language skills to participate in the group /lecture, either in the primary language of the group or with additional language support provided. We will exclude primary caregivers whose children have been removed from their custody.

Inclusion criteria for facilitators are as follows: 1) aged 18 or older, 2) prior participation in a training workshop for the lecture/PLH-YC, 3) agreement to either deliver the lecture (one session) or PLH-YC (five sessions), 4) provision of consent to participate in the full study.

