### Study outcomes

#### Primary outcome

*Child aggressive behaviour* will be assessed with the respective subscale of the parent-report Child Behavior Checklist (CBCL) 1½–5 and 6–18 years old [43]. Parents rate the occurrence of certain behaviours of their child on a 3-point Likert Scale (0 = *not true* to 2 = *very true* or *often true*).

*Child externalising disorders* will be evaluated by using The Mini International Neuropsychiatric Interview for Children and Adolescents – Parent Version (MINI-KID-P) [44]. The MINI-KID-P will be used to assess whether the criteria (based on ICD-10 and DSM-5) for (a) Conduct Disorder (CD) (F91.1, F91.2, F91.9) or (b) Oppositional Defiant Disorder (ODD) (F91.3) are met (yes/no). The results of the two disorders will be combined to one binary total score with 0 = *no externalising disorder* and 1 = *current externalising disorder* (ODD or CD).

On three occasions between baseline and post-test assessments, Parent Daily Ratings (PDR) [45] will be used to monitor *child oppositional and aggressive behaviour problems* that occurred within the last 24 h (answer format: *did occur/did not occur*). In order to minimise drop-outs, we will only administer the oppositional and aggressive subscale (10 items + 2 positive items) instead of the full PDR. We excluded the last item from the subscale (“he/she pouts”) because this question caused translation problems in the three implementation countries. The item was not understood correctly by parents and assessors and thus did not result in valid answers. The PDR will be assessed over the phone three times between pre- and post-assessment.

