#### Secondary outcomes

*Child internalising problems* will be evaluated by using the internalising subscale of the parent-report versions of the CBCL 1½–5 and 6–18 years old [43]. The internalising subscale raw scores range from 0 to 62 (CBCL 1½–5 version; 31 items) and 0 to 64 (CBCL 6–18 version; 32 items) with higher scores indicating more problems.

*Parenting behaviours* will be assessed in four ways. The Laxness and Over-reactivity Subscales of the Parenting Scale will be used, measuring dysfunctional parenting practices [46]. Second, we apply self-reported measures of positive parenting and effective discipline (Parenting of Young Children Scale) [47]. Third, we will add five items from the Alabama Parenting Questionnaire (APQ) phone interview (three items for positive and two for negative parental behaviours) [48, 49] to the PDR phone assessment for assessing daily reports of effective parenting behaviour. The APQ answer format was adapted to fit the PDR format (*did occur/did not occur*). Fourth, child maltreatment will be assessed using the ISPCAN-Child Abuse Screening Tool – Trial-Children (ICAST-TC) [50].

For *parent-child relationship*, the Five-Minute Speech Sample (FMSS) [51, 52] will offer insight into caregivers’ attitudes and feelings about their child and the quality of the relationship. The parent is instructed to talk about his/her child for 5 min. The parent’s response will be audio recorded. The parent-report is then rated by trained coders, e.g. with regard to coherence, as an indicator for parent-child relationship [53]. We will also use the subscales Warmth and Criticism of the Family Affective Attitude Rating Scale (FAARS, [54]).

*Parental mental health* measures will tap into depression, anxiety, and stress symptoms by using the eponymous DASS-21 [55]. Three subscales can be derived, measuring caregiver symptoms of stress, anxiety, and depression (seven items each subscale). Total DASS scores range from 0 to 63, with subscales from 0 to 21.

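### As written, the cost-effectiveness ratio has no lecture term in cost or effect, although its stated objective is PLH-YC versus the lecture

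*Protocol article*

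**What the plan says.** The protocol article's section on cost-effectiveness analysis opens with a comparison: "The objective of this analysis is to evaluate the costs and cost-effectiveness of the PLH parenting programme vs. the lecture on parenting". The aims in the overview section agree: "Examine the cost-effectiveness of PLH-YC in comparison to a lecture on parenting", with child aggressive behaviour as the outcome.

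The next sentence of the cost-effectiveness section defines the ratio: "Cost-effectiveness ratio will be calculated in terms of Euros per one point reduction of the CBCL aggressive subscale score in the PLH-YC programme". The same section adds the Parenting Scale, PARYC and CHU9D as further outcomes. It mentions the ratio again, with a cost-utility ratio, saying that these "will be calculated to assess and compare the cost-effectiveness of PLH-YC across sites and populations". That is a comparison between sites and populations, not between arms. Nowhere does the article use the word incremental or write a cost difference over an effect difference.

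For the same CBCL outcome, the section on primary and secondary outcome analyses does state an arm contrast: change in control participants against change in PLH-YC participants, controlling for pre-intervention level.

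**The concern.** A ratio built only from the PLH-YC arm cannot answer a question about PLH-YC against the lecture. Its denominator would be a before-after change, and that change contains whatever would have happened anyway.

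Two features of the design make a non-zero change in the lecture arm plausible. Families enter because the child scores at least 10 on a parent-reported scale, "as assessed with the oppositional defiant disorder subscale (ODD) of the Child and Adolescent Behavior Inventory", so natural improvement, and possibly regression to the mean, can be expected in both arms. The comparator is also active: parents in that arm attend a structured session of 1 to 1.5 hours.

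The result will be used. The article plans to base estimates of the resources for large-scale delivery in the three countries on the cost-effectiveness results. A ratio without its comparator could misstate what the programme adds over the cheaper alternative.

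**Working it through.** The article reports no cost or cost-effectiveness figure, so there is nothing to reproduce. The check is how far the literal ratio and the incremental ratio can differ.

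**Inputs**
- δ = 0.25 SD: the between-arm effect used in the sample size calculation.
- c: mean improvement in the lecture arm, in SD. Not given; assumed 0 to 0.50.
- r: lecture cost divided by programme cost, per family. Not given; assumed 0 to 0.5.
- P: programme cost per family. It cancels.

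**Formulas**
- Literal ratio: the PLH-YC arm improves by c + δ, so the ratio is P/(c + δ).
- Incremental ratio: (P − rP)/δ = P(1 − r)/δ.
- Incremental divided by literal: (1 − r)(c + δ)/δ.

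A factor above 1 means that the literal ratio makes the programme look cheaper per point than its added value over the lecture. A factor below 1 means the reverse.

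**Numbers put in (δ = 0.25)**
- r = 0.1, c = 0.25: 0.9 × 0.50/0.25 = 1.8
- r = 0.1, c = 0.50: 0.9 × 0.75/0.25 = 2.7
- r = 0.5, c = 0.25: 0.5 × 0.50/0.25 = 1.0
- r = 0.25, c = 0: 0.75 × 0.25/0.25 = 0.75

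| c (SD) | r = 0 | r = 0.1 | r = 0.25 | r = 0.5 |
|---|---|---|---|---|
| 0 | 1.00 | 0.90 | 0.75 | 0.50 |
| 0.10 | 1.40 | 1.26 | 1.05 | 0.70 |
| 0.25 | 2.00 | 1.80 | 1.50 | 1.00 |
| 0.50 | 3.00 | 2.70 | 2.25 | 1.50 |

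**Which part of the table is more likely**

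The article gives staffing but no costs. Under the online contingency plan, 12 PLH-YC parents need two groups × one facilitator × five sessions = 10 facilitator-sessions. Twelve lecture parents need one. PLH-YC facilitators have also had 40 hours of training and receive a 16-hour booster, against a brief training for the lecture. This points to a small r, and 1/10 = 0.1 is a reasonable illustration, but it counts staffing only and is not a costing.

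The two ratios agree when c = δr/(1 − r). At r = 0.1 that is 0.25 × 0.1/0.9 ≈ 0.03 SD. Above that value of c, the literal ratio favours the programme.

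**The case against.** The strongest reply is that the sentence should be read in context. The line before it names the lecture as comparator, the aims do the same, and the CBCL outcome is analysed between arms elsewhere in the article. Reduction in the programme may simply mean reduction relative to the lecture, with the exact formula left to a fuller analysis plan. This stands in part. A reader might infer that the investigators have chosen an uncontrolled before-after ratio, and the article does not establish that. But the article does fix a definition, and that definition leaves out the comparator its own objective names. An analyst could follow it as written.

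A reader might also infer that the literal ratio must flatter the programme two- or threefold. The article does not support that, because the factor depends on r and c and can be 1 or less.

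Regression to the mean should not be pressed either. Selection is on the CABI, while the outcome is a different instrument, the CBCL, measured at a pre-assessment scheduled after eligibility screening. How far regression carries over to the CBCL, and how much has already occurred by baseline, is unknown.

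Finally, one might argue that a CBCL point is not a single unit, because two age forms are used. The ranges in the article are for another subscale ("The internalising subscale raw scores range from 0 to 62" on the younger form, 0 to 64 on the older). It gives none for aggression, and it does not say which form a child who turns six receives at follow-up. That argument is not supported for this ratio.

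**Conclusion.** The point holds as a conflict between the stated objective and the only stated definition of the ratio. Taken literally, the definition gives a within-arm ratio that credits shared improvement to the programme and ignores what the lecture costs.

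The size cannot be fixed from the article. Over the assumed ranges the factor runs from 0.50 to 3.00, and at r = 0.1 with c between 0.25 and 0.50 SD it is 1.8 to 2.7. These are illustrations resting on assumed r and c and on the planned δ. The staffing figures make a factor above 1 more plausible than one below it, but do not prove it.

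The matter concerns a secondary aim and does not affect inference on the primary outcome. It should still be corrected, because the result feeds scale-up estimates and the correction is small.

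**What to change.** Restate the ratio as:

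(mean cost per family in PLH-YC − mean cost per family in the lecture arm) / (baseline-adjusted between-arm difference in CBCL aggression, signed so that a larger reduction under PLH-YC is positive).

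Use the same incremental form for the Parenting Scale, PARYC and CHU9D ratios and for the cost-utility ratio in quality-adjusted life years. Comparisons across sites and populations should then compare incremental ratios.

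State that the cost diaries cover lecture set-up and delivery. The section on cost outcomes speaks of programme costs without naming the lecture, and the aims promise explicitly only that other service use will be reported for both conditions.

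The cost is a few sentences of wording and a little more costing work for the lecture. CBCL outcomes are already analysed in both arms. The headline ratio may become less favourable.
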